### 7.2.4 Procedures to account for missing data

All analyses will use intention-to-treat analyses. Missing values of outcome variables and covariates will be replaced using multiple imputation procedure with 10 sets of imputations assuming missing at random. Sensitivity analyses for the primary outcomes include: complete case analysis and per-protocol analysis.

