Unpaired t-test will be used to compare the changes in primary outcomes between two groups. If statistically significant differences in baseline demographic characteristics between groups are found, these significant covariates will also be adjusted in these primary analyses with Analysis of Covariates. In this case, both the unadjusted and adjusted results will be reported. Multiple regression analysis with the primary outcomes at the sixth visit will act as the dependent variable and independent variables, alongside with the secondary outcomes, will be employed to identify factors that may associated with myopia control effectiveness.

All analyses will use intention-to-treat analyses. Missing values of outcome variables and covariates will be replaced using multiple imputation procedure with 10 sets of imputations assuming missing at random. Sensitivity analyses for the primary outcomes include complete case analysis and per-protocol analysis. All analyses will be 2-tailed with a significance level of 5%.

The CONSORT Statement will guide the reporting of results.

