## 6.7 Withdrawal Criteria

Participants (or parents / guardians for participants <18 years of age) are free to withdraw from participation in the study at any time upon request. No further data will be collected on participants who withdraw themselves from this study. If significant intolerance to study treatment is suspected at any time after randomization, participants may be requested to withdraw from the study at any time.

An investigator may discontinue or withdraw a participant from the study due to the following reasons:

- Significant study intervention noncompliance: unable to contact via three phone calls, more than three attempts to arrange missed follow-up appointments, wearing the spectacles less than five days a week and / or weekly average less than five hours/day.
- If any clinical adverse event or situation occurs (e.g. allergies to eye drops, reduction of visual function such as diplopia, reduction of BCVA; subject to clinicians’ judgement) such that continued participation in the study would not be in the best interest of the participant.
- If the participant meets an exclusion criterion (either newly developed or not previously recognized) that precludes further study participation.

Should participants require discontinuation of study treatment for any reason, or if they select to cease taking treatment, follow-up visits and data collection will not be continued as scheduled. The reason of discontinuation or withdrawal of participant from the study will be recorded on the Discontinuation / Withdrawal Case Report Form (CRF W) in Research Electronic Data Capture (REDCap). The use of REDCap can help reduce human errors in the randomization process, to assist data collection, and to provide a real-time dashboard for monitoring the project progress. Participants who sign the informed consent form, and are randomized but do not receive the study intervention may be replaced. If there are participants who signed the informed consent form, are randomized and received the study interventions but discontinue or withdraw within the first two weeks due to inability to meet inclusion criteria (e.g. unable to tolerate spectacles or eyedrops), and it is still within the recruitment period, then randomization of these participants will be discarded and replaced with a participant from the next allocation. All spectacles and eye drop (used or unused) will be returned to the investigator on withdrawal or discontinuation from the study.

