# 7. Statistical Considerations

## 7.1 Sample Size

In the study regarding low dose atropine for myopia control, mean change in refractive error after one year was 0.64 ± 0.56D (mean ± SD) (10). Our previous randomized clinical trial showed DIMS slowed down myopia progression by approximately 60% (8). The sample size is calculated based on an assumption that, adopting atropine and DIMS together will result in a 60% reduction of mean refractive error change relative to using only atropine, the difference detected between two groups (atropine alone vs. atropine and DIMS) will be 0.384 (0.64 x 60% = 0.384), and the effect size will be 0.685 (0.384/0.56 = 0.685). According to power analysis (G*Power Version 3.1.9.2), 46 subjects are required per group to achieve 90% power with a significance level of 0.05 (two-tailed). Assuming the dropout rate will be 20%, 56 subjects will be required for each group in this proposal. Therefore, 112 subjects (56 subjects × 2 groups) will be required for the entire study.

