### 7.2.2 Treatment effects

The effectiveness of myopic control will be calculated as:

1 – (progression therapy) / (progression control)

Unpaired t-test will be used to compare the changes in primary outcomes between two groups. If statistically significant differences in baseline demographic characteristics between groups are found, these significant covariates will also be adjusted in these primary analyses with Analysis of Covariates. In this case, both the unadjusted and adjusted results will be reported. Multiple regression analysis with the primary outcomes at the final visit will act as the dependent variable and independent variables, alongside with the secondary outcomes, will be employed to identify factors that may associate with myopia control effectiveness.

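### Ten imputations are valid for the primary analysis, but with 20% dropout and no stated seed a p-value near 0.05 does not repeat well; 100 imputations and a recorded seed cost almost nothing

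*Combined protocol and SAP*

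**What the plan says.** Section 7.2.4 states "All analyses will use intention-to-treat analyses" and fills in missing outcomes and covariates by a "multiple imputation procedure with 10 sets of imputations assuming missing at random". The Statistical Methods part of the Overview repeats the number: missing values "will be replaced using multiple imputation procedure with 10 sets of imputations". The imputed analysis is therefore the primary one. The alternatives are secondary: "Sensitivity analyses for the primary outcomes include: complete case analysis and per-protocol analysis".

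The primary test is simple: "Unpaired t-test will be used to compare the changes in primary outcomes between two groups" (section 7.2.2), two-tailed at 5% (section 7.2).

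Section 7.1 gives the expected loss: "Assuming the dropout rate will be 20%, 56 subjects will be required for each group in this proposal". Section 6.7 makes it likely that those children lack an 18-month value, because after discontinuation "follow-up visits and data collection will not be continued as scheduled". Section 9.1.2 does require follow-up visits after withdrawal for an adverse event, so a few may have later data.

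The document gives no random seed, imputation model, reason for choosing 10, or check of Monte Carlo error. Section 7.2 refers to a statistical analysis plan to be agreed by the Steering Committee, which could add these.

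**The concern.** Multiple imputation draws random values, so its result depends partly on the seed. The usual defence of a small number of imputations is relative efficiency. With a fraction of missing information (FMI) of 0.20 and m = 10 this is 1/(1 + 0.20/10) = 0.98. That figure describes the variance of the point estimate. It does not show how closely the p-value repeats when the same data are imputed again.

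At stake is the reading of a result close to 5%. Two analysts who follow the plan exactly on the same data could then report opposite conclusions for a primary outcome, and the documents would not say which run counts.

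**Working it through.** **Inputs from the plan.** SD of change 0.56 D, planned difference 0.384 D (0.64 × 60%), 46 evaluable and 56 recruited per group, 20% dropout (section 7.1); two-tailed 5% (section 7.2); m = 10 (section 7.2.4).

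**Inputs assumed.** Values missing completely at random; normal-model imputation; an auxiliary variable (such as an earlier visit's value) that is absent or correlated 0.7 or 0.8 with the outcome; smaller true effects of 0.24 and 0.256 D.

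**1. The plan's own figure.** Effect size 0.384/0.56 = 0.685. The two-sample t-test needs 45.8, so 46 per group, with 90.1% power. The stated 46 reproduces. Twenty per cent of 56 is 11.2, so about 11 are missing per arm.

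**2. Hand calculation at z = 1.96, FMI = 0.20.** Two parts of the pooled statistic vary with the seed.

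- The pooled estimate, with SD on the z scale √(FMI/m): √(0.20/10) = 0.141 at m = 10 and √(0.20/100) = 0.045 at m = 100. Taken alone, this spreads p over about 0.025 to 0.092 and 0.041 to 0.061.
- The pooled standard error, because the between-imputation variance is itself estimated from m draws. Its approximate contribution is 1.96 × ½ × FMI × √(2/(m − 1)): 1.96 × 0.5 × 0.20 × √(2/9) = 0.092 at m = 10, and 1.96 × 0.5 × 0.20 × √(2/99) = 0.028 at m = 100.

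Combined, the SD is √(0.141² + 0.092²) = 0.169 at m = 10 and √(0.045² + 0.028²) = 0.053 at m = 100. Then z = 1.96 ± 1.96 × 0.169 runs from 1.63 to 2.29, so p runs from 0.103 to 0.022. At m = 100, z runs from 1.86 to 2.06, so p runs from 0.063 to 0.039.

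**3. Simulation.** Set-up A: 3000 trials per setting, 11 missing per arm, imputation within arm, Rubin pooling with small-sample degrees of freedom, each trial analysed with two independent seeds. Its borderline ranges come from 60 datasets with p of 0.045 to 0.055 at 3000 imputations, each re-imputed 60 times. Set-up B: 600 trials per setting, each value missing with probability 0.2, 60 seeds per trial and a 6000-imputation reference; borderline means a reference p of 0.04 to 0.06.

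| Quantity | Auxiliary | m = 10 | m = 100 |
|---|---|---|---|
| 95% seed range of a p near 0.05, A | none | 0.022–0.114 | 0.038–0.065 |
| Same, A | 0.7 | 0.028–0.090 | 0.041–0.061 |
| Same, B | none | 0.024–0.108 | 0.039–0.062 |
| Same, B | 0.8 | 0.031–0.080 | 0.042–0.056 |
| Two seeds disagree, 0.384 D, A | none | 4.2% | 1.1% |
| Same, A | 0.7 | 2.5% | 0.7% |
| Same, B | none | 4.6% | 1.6% |
| Same, B | 0.8 | 1.4% | 0.4% |
| Two seeds disagree, 0.24 D, A | none | 8.4% | 2.3% |
| Same, A | 0.7 | 4.9% | 1.4% |
| Two seeds disagree, 0.256 D, B | none | 8.1% | 2.8% |
| Same, B | 0.8 | 4.6% | 1.5% |

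Repeats of set-up A at 0.384 D and m = 10 gave 3.8% to 4.5% without an auxiliary variable and 2.4% to 2.9% with correlation 0.7. In set-up B without an auxiliary variable, about 40% of seeds gave the minority verdict in a borderline trial at m = 10.

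**4. Validity.** Simulated type I error at m = 10 was 4.3% to 4.9% against a nominal 5%. Power at 0.384 D was 87.5% with 10 and 88.6% with 100 in one run, and 89.0% and 89.3% in another.

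**The case against.** The strongest reply is that nothing is wrong with m = 10. Rubin's rules already allow for a finite number of imputations through the (1 + 1/m) factor and the degrees of freedom. That stands. A reader might infer from the wide p ranges that the primary analysis is biased or its interval too narrow; the type I error in step 4 shows neither. Nor is there a power argument, since the loss is about one point or less.

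The wide ranges are also conditional on a borderline result. In set-up B only 2% to 4% of trials at 0.384 D had a reference p of 0.04 to 0.06, and more than 95% of seed pairs agreed. It would be wrong to infer that the verdict is likely to turn on the seed. The smaller effects are assumptions, although the Overview accepts that the combined effectiveness is unknown.

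The case with no auxiliary variable is the least favourable. The schedule in section 6.12 measures cycloplegic refraction and axial length at 6 and 12 months, so many dropouts would have earlier values. However, section 7.2.4 does not commit to using them, and a correlation of 0.7 to 0.8 narrows the range without removing the problem.

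A reader might also infer that an analyst could re-impute until p fell below 0.05 without detection. The documents do not support this. The complete-case analysis in section 7.2.4 uses no seed, and at 0.384 D without an auxiliary variable its verdict differed from the m = 10 verdict in only 2.8% of trials, so a discrepancy would stand out.

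Finally, the promised analysis plan could supply a seed and an imputation model. That is fair for those items. It does not settle the number of imputations, which the protocol itself sets at 10.

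**Conclusion.** The point holds as a matter of repeatability. Ten imputations give a valid primary analysis whose p-value is needlessly noisy near 5%: roughly 0.02 to 0.11 across seeds, or 0.03 to 0.09 with a moderately informative interim value, against roughly 0.04 to 0.065 with 100. Opposite verdicts from two seeds are uncommon at the planned effect (about 4%, or 2.5 to 3% with correlation 0.7) and more frequent at 0.24 D (about 5 to 8%). With 100 imputations they fall to about 1% and to about 1.5 to 2%.

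The sizes rest on 20% loss, missingness completely at random, a normal imputation model and the assumed correlations. With 10% or 30% missing, the m = 10 disagreement at 0.256 D without an auxiliary variable was 5.5% or 10.6%. Only refraction was simulated, because the documents give no SD or planned effect for axial length. The hand calculation depends only on FMI and m, so a borderline axial length result would show a similar spread for the same FMI.

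**What to change.** In section 7.2.4 and in the Overview's Statistical Methods, replace 10 sets of imputations with 100. State that the random seed is fixed and recorded before unblinding, and that the Monte Carlo error of the pooled treatment difference is reported beside the primary result. The two changes do different work: the larger number reduces dependence on the seed without removing it, and the recorded seed makes the result exactly reproducible. The figure of 100 is a judgement based on the spread shown above; the documents contain no precision target from which to derive it.

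The cost is one sentence in each place and a little computing time in SPSS for 112 children. Sample size, visits and the primary test are unaffected, and there is no statistical downside.

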### 7.2.5 Interim analyses

No formal interim efficacy analyses of the outcome data are planned, as it seems unlikely that there would be sufficient data and reason to terminate the trial early.

## 7.3 Data management

### 7.3.1 Source data

The source documents are CRF entries. This includes CRFs available in Research Electronic Data Capture (REDCap) and an electronic spreadsheet designed according to the forms in REDCap.

REDCap is a web application for building and managing online databases (21). Data stored within REDCap, information pertaining to the identity and activities of REDCap users are well protected. REDCap is installed under the IT infrastructure and environment in The Hong Kong Polytechnic University (PolyU). Both the web server and database server are located behind the firewall of PolyU. Multi-factor authentication is required for the users to gain access to the REDCap. User will need to connect to a dedicated virtual private network using Microsoft multi-factor authentication pre-registered and installed in their smartphone, and then enter use a different set of login and password to login REDCap. Each user has their own account for the REDCap access to the project. Limited access to various functionality and modules such as being able to export data, to enter data or to modify the user privileges could be set up according to the role of investigators. Data Access Group could be implemented to segregate users between HKU and PolyU so the users will only gain access to necessary items so as to protect the privacy of the subject. Access to the REDCap will be limited to trial staff only. Anonymized patient identifiers will be used on all trial-specific documents, other than the signed consent forms and electronic folder of the participant (only available to the unmasked investigators). The participants will be referred to by four code initials, date of birth and registration numbers, not by name.

### 7.3.2 Data Recording and record keeping

Direct access will be granted to authorised representatives from the team members from The Hong Kong Polytechnic University and The University of Hong Kong. All trial data will be collected by research optometrists and administration personnel and recorded directly on to paper copies of the CRFs or CRFs in REDCap. Data will then be entered into the study spreadsheets by authorised personnel at each site. Data will be backed-up onto a secure central cloud server. Only authorised, trained personnel will have access to the electronic data. The participants will be identified by a unique trial specific number and/or code in the spreadsheet. The name and any other identifying detail will not be included in any electronic files.

# 8. Ethical Approval and Consent

## 8.1 Ethics Approval

The researchers will seek ethical approval from Institutional Review Board of the University of Hong Kong/Hospital Authority Hong Kong West Cluster (HKWC/HKU Cluster IRB), and The Institutional Review Board of the Hong Kong Polytechnic University, prior to recruiting participants to the study.

## 8.2 Informed Consent

All participants will be given a copy of their written consent details and a participant information sheet. The consent form will be signed by both the participant, their parents/ guardians and an authorised researcher at the beginning of the first clinic visit. All data collected will be treated as confidential and electronic data will be stored securely at the Hong Kong Polytechnic University. The trial staff will ensure that the participants’ anonymity is maintained.

# 9. Assessment of Safety/Adverse Event Reporting

## 9.1 Adverse Events

### 9.1.1 Definition of an Adverse Event

Adverse event (AE) means any unfavourable and unintended sign including any abnormal laboratory finding, symptom or disease associated with the use of an intervention in humans, whether or not considered intervention-related, during the course of the study. Any incident associated with the eye drop will be recorded and reported through the same system as an AE (CRF AE in REDCap).

### 9.1.2 Contact for Notification of Adverse Events

Worsening of visual acuity, development of visual disturbances (such as diplopia, ghosting, glare), eye strain symptoms, symptoms of eye infection or allergic responses (such as redness, pain, decreased vision, discharge, increased light sensitivity) are to be noted on the Case Report Form (CRF AE) in REDCap. The relationship of each adverse event to the trial treatment must be determined by a clinically qualified individual according to the following definitions:

- **Related:** The adverse event follows a reasonable temporal sequence from trial treatment. It cannot reasonably be attributed to any other cause.
- **Not Related:** The adverse event is probably produced by the participant’s clinical state, by other modes of therapy administered to the participant or is otherwise unrelated to the trial treatment.

All AEs and other incidents occurring during the trial that are observed by study personnel or reported by the participant will be recorded on the CRF in REDCap, whether or not attributed to trial treatment. The following information will be recorded: description, date of onset and end date, severity, assessment of relatedness to trial intervention, other suspect drug or device and action taken. Follow-up information should be provided as necessary. The severity of events will be assessed on the following scale:

- **Mild (1):** Events require minimal or no treatment and do not interfere with the participant’s daily activities.
- **Moderate (2):** Events result in a low level of inconvenience or concern with the therapeutic measures. Moderate events may cause some interference with functioning.
- **Severe (3):** Events interrupt a participant’s usual daily activity and may require systemic drug therapy or other treatment. Severe events are usually potentially life-threatening or incapacitating. Of note, the term “severe” does not necessarily equate to “serious”.

These data on adverse event reports will be tabulated in a spreadsheet and reviewed quarterly at the Study Management Committee meetings.

Information to be collected includes event description, time of onset, clinician’s assessment of severity, relationship to study product (assessed only by those with the training and authority to make a diagnosis), and time of resolution or stabilization of the event. All AEs occurring while on study must be documented appropriately regardless of relationship. All AEs will be followed to adequate resolution. An appointment will be arranged for four to six weeks following AE resolution to check for any recurrence or changes as a result of the AE. Changes in the severity of an AE will be documented to allow an assessment of the duration of the event at each level of severity to be performed. AEs characterized as intermittent require documentation of onset and duration of each episode. These will be followed-up and assessed by medically fit clinician. It will be left to the judgement of the Steering Group to decide whether or not an AE is of sufficient severity to require discontinuing the participant from the study. A participant may also voluntarily withdraw from participating in the study due to what he or she perceives as an intolerable AE. If either of these occurs, the participant must undergo follow-up visits for trial assessment and be given appropriate care under medical supervision until symptoms cease, or the condition becomes stable.

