## 6.11 Secondary Outcome Measure

The secondary outcome measures are accommodative amplitude and response, pupil size, other ocular biometrics, which will be collected during first-, sixth-, twelfth- and 18^th^-month visits. Treatment compliance is checked by self-reporting log by participant at all the time points. Instillation of eye drop is checked by self-reporting log at all the time points. Information regarding to any adverse events or intervention events and whether they are related to the active treatment will be collected at all the time points.

All other measurements will be classified as exploratory outcomes.

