## 13.6 Reporting Schedule

The project coordinator will provide annual reports of study progress to the approving authorities stated in section 7.1. All serious adverse events that are fatal or life-threatening and suspected of being related to the treatment used in the trial will be reported to the local ethics committee within 72 hours.

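### The two relatedness categories for adverse events are not exhaustive: a possibly related event fits neither, so the relatedness item will be coded inconsistently

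*Combined protocol and SAP*

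**What the plan says.** Section 9.1.2 makes the causality judgement compulsory: "The relationship of each adverse event to the trial treatment must be determined by a clinically qualified individual according to the following definitions". Two definitions follow.

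- *Related* has two conditions. The first is timing: "The adverse event follows a reasonable temporal sequence from trial treatment". The second excludes rival explanations: "It cannot reasonably be attributed to any other cause".
- *Not Related* has two alternatives. The main one opens "The adverse event is probably produced by the" and goes on to name the participant's own condition or other therapy. The residual one reads "or is otherwise unrelated to the trial treatment".

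There is no possible, probable or unknown level.

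Relatedness is then used in three places, in three different terms. Section 6.11 makes it part of a secondary outcome: information on events and "whether they are related to the active treatment will be collected at all the time points". Section 13.6 sends to the ethics committee, within 72 hours, serious events that are "fatal or life-threatening and suspected of being related to the treatment used in the trial". Section 7.2.3 ties stopping of treatment to events it calls treatment-related. No section says how these terms correspond to the two categories.

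**The concern.** If assessors must code every event but the definitions leave some events without a code, the result depends on the assessor. One will reason that treatment was not excluded and choose *Related*. Another will note that the strict second condition fails and choose *Not Related*.

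This matters more here than in a placebo-controlled trial. Under Experimental groups in the Overview, both arms receive 0.01% atropine twice daily, so comparing the arms cannot isolate atropine reactions. Event-by-event causality coding is the main information the trial will hold on them.

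Rival causes are also built into the procedures. Section 6.9 has a topical anaesthetic and cyclopentolate, itself an antimuscarinic, instilled in both eyes, and section 6.12 schedules cycloplegia at baseline and at 6, 12 and 18 months. Several events listed in section 9.1.2, such as redness and light sensitivity, could have a reasonable second candidate around those visits. The same section asks for any other suspect drug or device to be recorded. It therefore expects more than one suspect, yet naming a reasonable second one rules out *Related*.

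**Working it through.** The plan gives no figure to reproduce. The check has three steps.

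**Step 1: are the definitions exhaustive?** Write them as conditions:

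- *Related* = timing plausible AND no other reasonable cause.
- *Not Related* = another cause probable OR otherwise unrelated.

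| Case | Timing | Other cause | Meets *Related*? | Meets *Not Related*? |
| --- | --- | --- | --- | --- |
| A | plausible | none reasonable | yes | no |
| B | plausible | probable | no | yes |
| C | plausible | reasonable but not probable; treatment not ruled out | no | no |
| D | any | treatment ruled out by the assessor | no | yes (residual alternative) |

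Case C is the gap. The residual alternative does not close it: it applies only once the assessor has decided that the event is unrelated, and in case C that is exactly what is undecided.

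**Step 2: what depends on the category?**

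- Independent of it: the definition of an adverse event (section 9.1.1); recording, where section 9.1.2 says events "will be recorded on the CRF in REDCap, whether or not attributed to trial treatment"; follow-up to resolution and quarterly committee review (section 9.1.2); notification of all serious events to the Study Management Committee within 72 hours (section 9.2.4); periodic safety updates (section 9.3); and the summary of all serious events by arm (section 7.2.3).
- Dependent on it, or on an unmapped synonym: the section 6.11 relatedness item, the section 13.6 ethics report, and the stopping of treatment in section 7.2.3.

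**Step 3: can the effect be sized?** Let p be the share of true reactions that fall in case C, and q the share of those coded *Not Related*. The under-count of related events is then p × q. The documents give neither. Taking p from 25% to 75% purely as an assumption:

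- q = 1: under-count = p × 1 = 25% to 75%.
- q = 0: under-count = p × 0 = 0.

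The range therefore runs from 0 to 75% and only restates what was put in. In the other direction, case C events that are not true reactions but are coded *Related* would raise the count.

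**The case against.** A reader might infer that possibly related events are lost from safety reporting. The documents contradict this: every provision in the first group of step 2 applies without regard to relatedness.

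A reader might also infer that the ethics report is under-counted. Section 13.6 uses the wider standard of suspicion, which on its own terms covers a possible relation, and it does not refer back to the *Related* code. It also covers only fatal or life-threatening events, not redness or eye strain. An event would be missed there only if someone read suspicion as the strict category. The documents neither say so nor rule it out.

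Nor do they support saying that hardly any event could be *Related*. The test is whether another cause is reasonable, not merely conceivable, and a clinically qualified person applies it.

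Finally, section 7.2 plans no analysis of related-event incidence; section 7.2.3 summarises discontinuations and serious events. Section 6.11 says only that relatedness will be collected.

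These objections stand and set the limits of the point. They do not close case C: a compulsory item that belongs to a named secondary outcome still has no valid code for a common kind of causality judgement. That section 7.2 is silent on relatedness does not help, since it leaves open how the item will be reported.

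**Conclusion.** The point holds in narrow form. The two categories in section 9.1.2 are not exhaustive, and *Related*, the suspicion standard in section 13.6 and the treatment-related wording in section 7.2.3 are not mapped to one another. The consequences are inconsistent coding of the section 6.11 relatedness item, with possible under-counting because the strict wording of *Related* leans that way, and ambiguity in the steps that rely on relatedness. The direction is likely rather than established, and no percentage should be attached to it.

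This is a minor drafting fault. The primary efficacy comparison does not use relatedness, and general safety recording is intact. The conclusion assumes that the case report form follows the section 9.1.2 definitions; the form is not in the documents, so a third option on it cannot be excluded.

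**What to change.** Make the categories exhaustive in section 9.1.2 and on the adverse event form. One way is to add *Possibly related*, for plausible timing with treatment neither ruled out nor the only reasonable cause, and to define *Not Related* so that every remaining event falls into it. State that *Possibly related* counts with *Related* when the section 6.11 outcome is reported and when the suspicion standard in section 13.6 is applied.

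The cost is protocol and form wording. Section 2 records the trial as not yet recruiting, so on the document's own account this can be done before any event is coded. The downside is that more events will be classed as related, some of them not true reactions. Reporting the two levels separately as well as combined would keep that visible.

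The change should not be carried into section 7.2.3 by default. Widening what counts as treatment-related there could widen the stopping of treatment, and section 6.7 ends scheduled follow-up and data collection once treatment stops, which would add missing primary outcome data. Section 9.1.2, by contrast, leaves discontinuation for an adverse event to the Steering Group's judgement and requires follow-up visits afterwards. Sections 6.7, 7.2.3 and 9.1.2 must be reconciled with one another and with the revised categories. No discontinuation rule is proposed here.
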